#### Qualitative interviews

At or towards the end of their sessions with their Community Navigator (after a minimum of five sessions have been received, or the participant has elected to discontinue meetings with their Community Navigator), a researcher will contact participants for a qualitative interview. Members of the team who will be carrying out the interviews with participants have personal experience of depression and anxiety, and topic guides for all qualitative work will be coproduced with the study working group. These interviews will explore people’s experiences of the programme, including:The content of sessions with Community NavigatorsThe impact of being part of the programmeHow the programme proved helpfulChallenges around being part of the programmeSuggested improvements to the programme

Qualitative interviews will be conducted with participants (*n* = 20), Community Navigators (*n* = 3) and up to ten other stakeholders. These could include the Community Navigators’ supervisors, other clinicians, social care or voluntary sector staff such as peer support workers, and family and friends nominated by participants as important to them in utilising the support. We will purposively sample 20 participants receiving the intervention for a qualitative interview as far as possible to ensure representation from all services and participants with a range of demographic and clinical characteristics, including those who completed the programme of Community Navigation and those who discontinued the intervention early.

These interviews will be used to refine a Theory of Change for this programme. This is a model which outlines the processes by which the programme may have an effect [50]. The Theory of Change will be built around the following components:Assumptions - the context in which the programme is taking place and how it will workInputs - the resources put in to deliver the programmeActivities - the content of the programmeEnablers - factors facilitating the delivery of programme outcomesIntermediate outcomes – the shorter-term changes or impacts of the programmeFinal goals – the broader-longer term aims of the programme

#### Process recording

To facilitate examination of the intervention content, Community Navigators will complete session logs following each session with a participant, detailing the location of the meeting and its content (selecting from a list of planned types of support). Feedback will be sought from intervention-arm participants for two of their Community Navigation sessions. Participants will be contacted as soon as possible (ideally within 3 days) following a randomly selected session and asked questions over the phone by a study researcher. Questions, taken from a standard feedback form, will cover the location of the meeting, what types of support were provided (with the same options as in Community Navigators’ session logs), and a rating of how they found the session on a five-point scale (from very good to very poor). The aim is to have data spanning all ten sessions without having to ask participants for feedback after each session.

### Data analysis

Factors relating to the acceptability of the intervention and the feasibility of trial procedures, and completion rates for potential primary and secondary outcomes in a definitive RCT will be reported.

Feasibility will be assessed by:Recruitment duration; the time period from recruitment of the first trial participant to meeting the trial recruitment target (40 participants).Recruitment; the number of participants screened, the number of those screened who are eligible, and the number of eligible participants who consent to participate in the study by four months.Attrition; the number of participants who consent to participate that remain in the study until the end of follow up at six months.Intervention take-up rate for those in the intervention arm: the proportion of participants who met their Community NavigatorImplementation of the intervention: the proportion of participants that maintained engagement with a Community Navigator and the number of sessions of support provided. A minimum threshold of at least three meetings with a Community Navigator has been set to represent treatment as per protocol.Number of adverse events recorded in each study arm until the end of follow up at six months.

#### Quantitative measures

We will report rates of missing data and summary statistics for all outcomes, both overall and by randomised group, at baseline and at follow-up. This trial will be too small to make clear inferences about observed differences between groups. However, for two candidate primary outcome variables for a future definitive trial: loneliness (measured using the 11-item De Jong Gierveld Loneliness Scale [41]) and depression (measured with the PHQ-9 [46]), we will calculate an effect size (non-standardised mean difference between groups) with confidence intervals, to assess the potential for the intervention to affect outcomes.

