### Participants

At each study site, 20 service user participants will be recruited at baseline (total *N* = 40). This sample size has been chosen to be sufficient to give an indication of the acceptability of the Community Navigator programme and the feasibility of trial recruitment procedures. The treatment group will consist of 30 participants and the remaining 10 participants will form the control group.

To ensure that we are working with a population who are experiencing loneliness, we will use the six-item De Jong Gierveld Loneliness Scale [27] as a screening measure, for which a score of 2 has been established as a minimum threshold for loneliness. De Jong Gierveld and colleagues recommend categorising scores of 2 to 4 on this scale as moderately lonely and 5 to 6 as severely lonely [28]. Other inclusion criteria have been kept deliberately broad, although we will prioritise service users currently receiving support from several disciplines (e.g. care coordination, psychology and medical review), to help us explore whether Community Navigation is a useful addition to multi-disciplinary care from a secondary mental health service.

Inclusion criteria:Currently on the caseload of a secondary mental health service for people with depression or anxietyAged 18 years or olderScore at least 2 on the six-item De Jong Gierveld Loneliness Scale [27] at initial screening

Exclusion criteria:People who do not have capacity to consent to participatePeople who pose a risk of harm to others (as judged by their care coordinator) such that meetings with a researcher or Community Navigator are not recommendedPeople who are unable to communicate in English. Resources were not available to deliver this early stage intervention in other languagesPeople who are currently an inpatient at a mental health or general hospital or using mental health crisis services

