### Randomisation

Participants will be randomised to a treatment group (*n* = 30) or a control group (*n* = 10). Randomisation will be stratified by study site and will be 3:1 for intervention to control using block randomisation. An independent statistician in UCL Division of Psychiatry will generate the allocation sequence using Stata, which will be shared with the chief investigator. It will be concealed from the study researcher, who will be blind when recruiting participants and collecting baseline data. Once participants have completed the baseline questionnaires, the researcher will contact the chief investigator to ascertain the outcome of their randomisation. Due to limitations in the researcher resources available, participants’ allocations will not be concealed from the research team. The study researcher will contact participants to let them know the outcome of randomisation, send those in the control group information on local resources, and, for those in the intervention group, inform clinical supervisors that they are ready for allocation to a Community Navigator.

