### Outcome measures

#### Procedure

All participants in the feasibility trial will be asked to complete self-report questionnaires at baseline and at the six-month end of intervention follow-up, through a structured interview with a study researcher. Additionally, 20 participants receiving the intervention, the three Community Navigators and ten other stakeholders (the Community Navigators’ supervisors, and other involved mental health team staff and participants’ involved friends or family) will be asked to take part in a qualitative interview following the intervention. Interviews will explore acceptability of the community navigator programme and views on its impact from several perspectives. This is described in the SPIRIT flow diagram (Fig. 1) and the SPIRIT trial schedule (Table 1).

Information about all study assessments is provided in the participant information sheets, and consent to collect data and contact participants about follow-up is included in consent forms. Written consent from participants will be confirmed before the 6 month follow-up questionnaires are completed. A separate information sheet and written consent from participants will be provided for qualitative interviews. Participants will be offered a £20 gift in cash to thank them for their time at three time-points (upon completion of each of the baseline and follow-up questionnaires and the qualitative interview).

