#### Measures

A number of potential primary and secondary outcome measures for a future definitive RCT will be included. These self-report questionnaires will be assessed for response and completeness at baseline and six-month follow-up. The battery of measures for use in the study was reviewed and shortened following feedback from preliminary testing and discussion with the working group. Data collection will begin by asking participants for information on their socio-demographic characteristics including age, gender, ethnicity, marital status, living arrangements, accommodation, and employment. Participants will then be asked to complete the following validated outcome measures, all of which provide data for analysis in continuous form:The De Jong Gierveld Loneliness Scale is an 11-item, self-report measure of loneliness, yielding a total score and subscale scores for social and emotional loneliness [41].The Lubben Social Network Scale is a six-item self-report measure assessing quantity and quality of contact with family and friends [42].The Resource Generator UK is a 27-item measure of perceived access to social capital [43].The Time Budget Diary is a retrospective self-report measure of activity over the previous week [44]. Additional questions have been added to this measure so that participants are asked whether activities were done with others or alone and, if with others, whether this was online, phone or face-to-face. These additions will allow us to distinguish activity involving social contact from other activity.The Warwick-Edinburgh Mental Well-being Scale is a 14-item self-report scale of mental wellbeing [45].The Patient Health Questionnaire (PHQ-9)is a nine-item self-report measure of depression [46].The Generalized Anxiety Disorder Questionnaire is a seven-item self-report measure of anxiety [47].The EQ-5D-5 L is a five-item self-report health outcome measure [48].The Recovering Quality of Life Questionnaire is a 10-item self-report measure of quality of life developed for use across all mental health populations [49].

These measures were chosen by the working group after extensive discussion balancing data collection needs and respondent burden. They aim to capture dimensions which support from a Community Navigator may improve including mental health symptoms (depression, anxiety), social outcomes (loneliness, social network, social capital), day-to-day activity and general wellbeing (mental wellbeing, quality of life).

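### As stated, the loneliness and PHQ-9 comparisons do not use baseline score or site, which gives up precision if baseline and six-month scores are at least moderately correlated

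*Protocol article*

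**What the plan says.** The Quantitative measures section of the protocol article's Data analysis plans missing-data rates and summary statistics for every outcome, overall and by arm, at both time points. For two candidate primary outcomes, the 11-item De Jong Gierveld scale and the PHQ-9, it adds a between-arm comparison: "we will calculate an effect size (non-standardised mean difference between groups) with confidence intervals". The stated purpose is "to assess the potential for the intervention to affect outcomes". No model, covariate or stratum is named, and the only stated role for baseline scores is descriptive.

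Elsewhere the design supplies what an adjusted analysis needs:

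- Procedure: "All participants in the feasibility trial will be asked to complete self-report questionnaires at baseline and at the six-month end of intervention follow-up". The Randomisation section has the baseline questionnaires completed before the allocation is obtained.
- Measures: the scales are described as "all of which provide data for analysis in continuous form".
- Randomisation: "Randomisation will be stratified by study site and will be 3:1 for intervention to control using block randomisation".
- Participants: "The treatment group will consist of 30 participants and the remaining 10 participants will form the control group".

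**The concern.** On its ordinary reading, the stated estimator is the plain difference between the two arms' six-month means. That leaves out a pre-randomisation measurement of the same scale and the factor used to stratify allocation.

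Two things are at stake. The first is precision. If baseline predicts follow-up reasonably well, the interval is wider than the same data would allow. The second is how the one realised estimate is read. With only 10 controls, a noticeable chance difference in baseline means is quite likely, and part of it carries into the unadjusted six-month difference.

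This is the only between-arm effect estimate that the article states for an outcome measure, and it is meant to inform a future definitive trial.

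**Working it through.** **Inputs from the protocol article.** Total 40, ratio 3:1, 20 per site (Participants, Randomisation). The split reproduces: 40 × 3/4 = 30 and 40 × 1/4 = 10, or 15:5 within each site of 20. No SD, power, confidence level or interval width is stated, so there is no precision figure to reproduce.

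**Assumptions not in the document.** 95% confidence, a common SD, a baseline to six-month correlation r between 0 and 0.7 and, for the 24 v 8 case, 20% loss in each arm. Results are in units of the outcome SD.

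**Step 1: unadjusted half-width.** SE = sqrt(1/30 + 1/10) = 0.365. Half-width = t(0.975, 38) × SE = 2.024 × 0.365 = 0.739. With 24 v 8 it is 0.834.

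**Step 2: half-width adjusted for baseline and site.** Half-width = t(0.975, 36) × sqrt[(1 − r²) × (1/30 + 1/10) × (1 + 2/35)]. The last factor is the expected cost of chance association between arm and two covariates. It slightly overcharges here, because site is balanced by design.

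| r | 30 v 10 | against 0.739 | 24 v 8 (unadjusted 0.834) |
|---|---|---|---|
| 0 | 0.761 | 3% wider | 0.867 |
| 0.2 | 0.746 | 1% wider | 0.849 |
| 0.3 | 0.726 | 2% narrower | 0.827 |
| 0.5 | 0.659 | 11% narrower | 0.751 |
| 0.7 | 0.544 | 26% narrower | 0.619 |

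**Step 3: break-even for 30 v 10.** Setting step 2 equal to step 1 gives 1 − r² = (2.024/2.028)² / (1 + 2/35) = 0.942, so r is about 0.24.

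**Step 4: chance baseline imbalance.** The difference in baseline means has the same standard error, 0.365 SD. The probability that it exceeds 0.3 SD in either direction is 2 × (1 − Φ(0.3/0.365)) = 41%; for 0.5 SD it is 17%. Given an imbalance d, the unadjusted six-month difference shifts by r × d. For d = 0.5 SD the shift is 0.15, 0.25 or 0.35 SD at r = 0.3, 0.5 or 0.7.

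**Step 5: simulation** (15:5 in each of two sites, 10,000 runs per setting). The mean half-width falls from 0.734 to 0.645 at r = 0.5 and from 0.736 to 0.534 at r = 0.7. Both estimators are unbiased, with coverage of about 94% to 96%. If sites differ by an assumed 0.5 SD, the unadjusted half-width rises to about 0.76; if they do not differ, including site brings no gain.

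**The case against.** The strongest reply is that the text does not exclude adjustment. *Non-standardised* means expressed in scale points rather than divided by the SD, so a covariate-adjusted difference also fits the description. A condensed article may leave covariates to the full protocol or analysis plan. This stands against any claim that the investigators chose to reject adjustment. It does not remove the point: the article does name its estimator, and as worded it is the less efficient one unless the correlation is low.

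A reader might infer that the unadjusted estimate is biased or its interval invalid. Neither follows. Under randomisation the estimate is unbiased, and the interval already allows for chance imbalance, as the simulated coverage shows. What remains is lost precision and sensitivity of this single estimate to the imbalance that happens to occur.

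A reader might also infer that site imbalance could distort the result. Blocked, site-stratified 3:1 allocation gives about 15:5 at each site, so apart from dropout it cannot do so materially.

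The gain also depends on a correlation that the document does not give. Entry requires at least 2 on the six-item loneliness scale, which restricts the baseline range and could lower r for loneliness; the PHQ-9 is not a screening criterion.

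Finally, the protocol itself says "This trial will be too small to make clear inferences about observed differences between groups", and the sample size rests on acceptability and feasibility. That limits the importance of the point, since even the adjusted intervals are wide.

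**Conclusion.** The point holds as a matter of efficiency, not validity. As stated, the comparison makes no use of the baseline score or the stratification factor, although both are available. With complete follow-up of 30 v 10, adjustment changes the 95% half-width from about 0.74 SD to between 0.76 SD (r = 0) and 0.54 SD (r = 0.7). It helps above r of about 0.24. The balance favours adjusting: a 3% loss at worst against an 11% to 26% narrower interval at r = 0.5 to 0.7. The correlations are assumed.

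Adjustment also removes, on average, the r × imbalance shift in the one estimate the trial will produce. That argument concerns the baseline score alone. Site belongs in the model because it is the stratification factor, with a small gain only if sites differ.

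The change is worth making but is not critical. The estimate stays exploratory either way.

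**What to change.** In Quantitative measures, state that for each of the two scales a linear model of the six-month score will be fitted on arm, the baseline score of the same scale and site. The adjusted mean difference in scale points with its 95% CI is the main exploratory estimate, and the unadjusted difference is reported beside it. If the full protocol or analysis plan already specifies this, one clause saying so is enough. Keep the existing caution about clear inference.

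The change needs no new data and no change to conduct. It uses two degrees of freedom. If the correlation is near zero, the interval is about 3% wider with 30 v 10 and about 4% wider with 24 v 8 (0.867 against 0.834).

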#### Qualitative interviews

Data will be analysed using a thematic analysis approach [51], with involvement from members of the working group. We will hold analysis meetings to review transcripts, develop coding frames, and review themes. Some of those who will be involved in qualitative interview analysis have personal experience of depression and anxiety. Expertise by experience will explicitly be drawn upon in the analysis process, following the McPin Foundation approach to peer research [52]. The research will thus benefit from combining research skills and lived experience in the analysis and synthesis of data [53]. Analysis will focus on understanding people’s experience of the intervention, what could be improved about it and informing the Theory of Change.

#### Process recording

Descriptive information from Community Navigators’ and participants’ process records will be reported to describe the content of the intervention. For sessions where both the Community Navigator and participant have completed session logs, levels of agreement on the types of activity undertaken in the session will be assessed and inter-rater reliability calculated using Cohen’s kappa [54]. This will provide an indication of the accuracy of Community Navigators’ reports of session content and demonstrate whether they view session contents differently to participants. Summary statistics of participants’ ratings of the quality of sessions with Community Navigators will also be reported.

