#### Intervention outline

Those receiving the intervention (*n* = 30) will be offered up to ten, hour-long meetings with a Community Navigator and access to up to three group sessions over a 6-month period alongside their standard care. Participants can have as many meetings as they want over the 6 months, up to a total of ten, and these meetings can be scheduled whenever they are most helpful within the 6 months. Each participant may use a budget of up to £100 on goals agreed with their Community Navigator to facilitate access to and participation in activities that provide opportunities for developing social connections. Meetings may take place in participants’ homes, community spaces or NHS premises, as the participant prefers.

The Community Navigation intervention will comprise three main components. Firstly, Community Navigators will build up rapport through discussing the person’s social network and interests. A social network mapping tool will be used to identify the people, places and activities that are important to the person. Items will be plotted in terms of importance and may be current, previous or potential new connections that the person would like to form. The aim is to collaboratively identify the person’s current interests and social connections, potential areas for new activity or social contact and how existing connections could be strengthened.

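### Agreement and Cohen's kappa do not measure the accuracy of Navigators' session reports and can look the same for one-sided over-reporting and for random disagreement; paired tick rates per support type should be reported beside them

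*Protocol article*

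**What the plan says.** Under Outcome measures, Process recording, Navigators log the content of every session by selecting from a list of support types. Participants are telephoned about a sample of sessions: "Feedback will be sought from intervention-arm participants for two of their Community Navigation sessions". The call comes soon after the session, "following a randomly selected session and asked questions over the phone by a study researcher", and offers the list of support types "with the same options as in Community Navigators’ session logs". The purpose of the sampling is coverage: "The aim is to have data spanning all ten sessions without having to ask participants for feedback after each session". Under Intervention outline, the number of sessions is the participant's choice: "Participants can have as many meetings as they want over the 6 months, up to a total of ten".

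Under Data analysis, Process recording, records from both sources are described. Where both reports exist for a session, agreement on the types of activity is assessed, with "inter-rater reliability calculated using Cohen’s kappa". Two uses are stated for this comparison. It should give some indication of how accurate the Navigators' reports are, and it should "demonstrate whether they view session contents differently to participants".

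**The concern.** The section names a statistic and says what it will show, so this is not a detail left to a later analysis plan. Neither stated use is well served.

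- **Accuracy.** This needs a reference standard. The comparator here is what a participant recalls on the telephone. Low agreement could reflect either party's error, and high agreement could reflect a shared one.
- **Viewing sessions differently.** The informative form of this question is whether Navigators tick a support type more or less often than participants do for the same sessions. Kappa treats the two raters symmetrically and does not report that difference. It also depends strongly on how common the support type is, and a list of planned support types is likely to contain both rare and near-universal ones.

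At stake is the description of what was delivered. If Navigators record planned content that participants do not recognise, that matters for a manualised intervention, and the two planned agreement summaries could look the same as for harmless noise.

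**Working it through.** The protocol gives no expected kappa or sample size for this comparison, so there is no figure to reproduce.

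**Inputs from the protocol.** The intervention arm is 30: "The treatment group will consist of 30 participants and the remaining 10 participants will form the control group". Two calls each gives at most 30 × 2 = 60 paired reports. Navigators log up to 30 × 10 = 300 sessions.

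**Assumptions.** Each support type is a separate yes/no item, level of agreement means percent agreement, all 60 pairs are obtained, and the 2×2 tables are illustrative.

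**Formulas.** Let a = both tick, b = Navigator only, c = participant only, d = neither, n = 60.
- Observed agreement: po = (a + d)/n
- Chance agreement: pe = [(a + b)(a + c) + (c + d)(b + d)]/n²
- Kappa = (po − pe)/(1 − pe)
- Tick-rate difference, Navigator minus participant = (b − c)/n
- Positive agreement = 2a/(2a + b + c); negative agreement = 2d/(2d + b + c)

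**Table A, one-sided** (30, 18, 0, 12): Navigators tick 48, participants 30 of those 48.
- po = 42/60 = 0.70; pe = 0.8 × 0.5 + 0.2 × 0.5 = 0.50; kappa = 0.20/0.50 = 0.40
- Difference = 18/60 = +30 percentage points
- Positive agreement 60/78 = 0.77; negative agreement 24/42 = 0.57

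**Table B, balanced** (21, 9, 9, 21): each side ticks 30.
- po = 42/60 = 0.70; pe = 0.50; kappa = 0.40
- Difference = 0
- Positive and negative agreement both 42/60 = 0.70

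The two planned summaries are identical in A and B, while the paired difference separates them. Treating the pairs as independent, its standard error is √[(b + c) − (b − c)²/n]/n. In A this is √(18 − 5.4)/60 = 0.059, so the 95% interval is about 18 to 42 points. In B it is √18/60 = 0.071, so the interval is about −14 to +14 points. Swapping b and c in A leaves po and kappa unchanged, so the direction is also invisible to them.

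**Table C, rare type** (1, 2, 2, 55).
- po = 56/60 = 0.933; pe = 0.05² + 0.95² = 0.905; kappa = 0.0283/0.095 = 0.30
- Positive agreement 2/6 = 0.33; negative agreement 110/114 = 0.96

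**Near-universal type** (48, 6, 6, 0).
- po = 0.80; pe = 0.81 + 0.01 = 0.82; kappa = −0.02/0.18 = −0.11
- The same 80% agreement with half of reports positive (24, 6, 6, 24) gives pe = 0.50 and kappa = 0.60

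**Secondary check, coverage of early stoppers.** The protocol does not say how sessions are drawn. Suppose two of session numbers 1 to 10 are drawn in advance. A participant who attends three gets no call with probability C(7,2)/C(10,2) = 21/45 = 47%, and at least one with 53%. Expected calls are 2 × 3/10 = 0.6, against 2.0 for someone attending ten. Each delivered session still has a 2/10 = 20% chance of selection, so session-level summaries are not distorted by the draw itself.

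**The case against.** The wording is modest: the protocol offers only an indication of accuracy, and asks whether views differ, not who over-reports. Kappa is not reported alone, so the rare-type example would appear with its 93% agreement beside it. Descriptive data from both sources are also planned, and tick rates of 80% against 50% might show there. Nothing says that kappa will be pooled across support types, and some of the proposed summaries are the kind of detail an analysis plan adds. No candidate outcome rests on this comparison.

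Most of this stands as a limit on severity. It does not remove the point. The percentage agreement rescues the rare-type example but not Tables A and B, where both planned summaries coincide. The descriptive reporting does not clearly fill the gap: Navigators log up to 300 sessions and participants report on at most 60, so unless the description is restricted to paired sessions, the two sets of tick rates refer to different sessions.

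A reader might go further and infer that the feedback cannot support its stated use at all, or that the sampling misses people who stop early. The documents do not support either. Agreement does speak to whether individual reports differ. The draw from sessions 1 to 10 is an inference, and even under it about half of those attending three sessions would be called. The qualitative interviews purposively include people who discontinued early, although they do not supply the structured session ratings. Nor does the protocol claim to show the direction of disagreement.

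**Conclusion.** The point holds, and it is minor. Against participant recall, agreement and kappa measure agreement only. They can be identical (70% and 0.40) for a 30-point one-sided difference in tick rates and for no difference at all. Kappa also falls to 0.30 at 93% agreement for a rare support type, and to −0.11 at 80% agreement for a near-universal one. The protocol's wording on accuracy therefore claims more than the method gives, and its question about differing views is better answered by a paired comparison.

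The numerical examples rest on invented tables, 60 complete pairs and yes/no scoring of each type. The general properties do not: kappa is symmetric between the raters and depends on prevalence whatever the data.

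The coverage of early stoppers is a secondary note. If sessions are chosen before attendance is known, these people are under-represented per person, but not excluded. The 47% figure is conditional on an assumed draw.

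**What to change.** In Data analysis, Process recording, restrict the comparison to sessions with both reports and give, for each support type:
- the paired 2×2 table;
- the Navigator-minus-participant difference in tick rates, with a confidence interval that allows for up to two reports per participant (for example, a bootstrap that resamples participants);
- positive and negative agreement;
- kappa as a supplement.

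Replace the statement about accuracy with one about agreement between Navigator and participant reports.

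For coverage, report how many participants gave no session feedback, by number of sessions attended. The draw itself need not change. Taking one call from sessions 1–3 and one from 4–10 may look attractive, but it would give selection chances of 1/3 and 1/7 instead of an even 1/5. That would require weighting and would work against the aim of spanning all ten sessions.

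The cost is a few more lines of descriptive analysis. No new data items are needed.
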